## Abstract

**Background:**

Neck pain caused by cervical spondylosis has become a common health problem worldwide among >40-year-old adults. Acupuncture intervention is one of the most popular treatment measures for this disorder. However, evidence for its efficacy in relieving neck pain and recovering neck physiological function has not been established in randomized, placebo-controlled trials. The primary aim of this trial is to assess the efficacy and safety of active acupuncture compared with sham acupuncture intervention for neck pain caused by cervical spondylosis.

**Methods/Design:**

We will conduct a randomized, double-blind, parallel-group, placebo-controlled trial comparing active acupuncture with placebo (sham acupuncture). A total of 456 patients with neck pain caused by cervical spondylosis who meet the eligibility criteria from outpatient clinics of the Second People’s Hospital of Fujian Province and the Affiliated Rehabilitation Hospital, Fujian University of Traditional Chinese Medicine will be recruited and randomized into an active acupuncture or sham acupuncture group. The participants will undergo treatment sessions with either active or sham acupuncture intervention five times a week for 2 weeks. Evaluation by blinded assessors at baseline and at intervention for 1 and 2 weeks will include demographic characteristics, validated questionnaires (Northwick Park Neck Pain Questionnaire (NPQ) scale, Short-Form 36 (SF-36) scale, and McGill pain scale), examination of neck physiological function, and adverse events. All included patients will be followed up and investigated for relapse of neck pain at 4, 8, and 12 weeks after intervention.

**Discussion:**

This paper describes the rationale and design of a randomized double-blind, placebo-controlled trial that aims to determine the efficacy and safety of acupuncture intervention for neck pain caused by cervical spondylosis. The primary outcomes are changes in the NPQ score and neck physiological function. Secondary outcome measures include quality of life, adverse events, and relapse of neck pain. If successful, this project will provide evidence of the efficacy and safety of acupuncture for neck pain caused by cervical spondylosis.

**Trial registration:**

Chinese Clinical Trial Registry: ChiCTR-TRC-12002206.

Registration date: 11 May 2012.

## Background

Cervical spondylosis (CS) is defined as age-related chronic disc degeneration. It is also defined as vertebral osteophytosis secondary to degenerative disc disease, which in the cervical spine may be asymptomatic or can present as pure axial neck pain, cervical radiculopathy, cervical myelopathy, or cervical myeloradiculopathy [1,2]. Neck pain caused by CS (CS neck pain) is associated with slight degenerative changes within the intervertebral disc in early CS [3]. CS is usually asymptomatic, but may present with symptoms of neck pain, neck stiffness, or even shoulder pain and stiffness. Its etiological factors are multifactorial and involve poor posture, anxiety, depression, neck strain, and sporting or occupational activities [4]. With acceleration of the pace of modern life, computers, air conditioning, fans, and cars have become widely used, and CS neck pain has become a common health problem worldwide. It is reportedly associated with a 50% incidence of radiological evidence in individuals over the age of 40 years and an 85% incidence of radiological evidence in individuals over the age of 60 years [5]. Neck pain is one of the most frequent issues among patients with CS. About two-thirds of adults in the UK reportedly experience neck pain at some time in their lives, with men more commonly affected than women, at a ratio of 3:2 [6]. A Norwegian survey of 10,000 adults showed that 34% of respondents had experienced neck pain in the previous year [7]. In Hong Kong, the prevalence of neck pain caused by CS is 15% to 17%, and the lifetime prevalence is 30% to 50% [8]. Approximately 33% of adults in Canada and 43% in Sweden had experienced neck pain in the past several months [9,10].

Non-surgical treatment is usually the most appropriate course of initial management. Most CS neck pain responds to conservative measures. Stress management or postural advice in daily activities, work, and hobbies is effective for some patients with slight neck pain. The current clinical treatments mainly include administration of non-steroidal anti-inflammatory drugs, muscle relaxants, physiotherapy, analgesics, and so on [11]. However, there is little evidence to support the efficacy of these therapies for CS neck pain. The most optimal treatment has not yet been established.

Traditional Chinese medicine measures, such as acupuncture, massage, neck exercises and so on have been extensively used for the management of CS neck pain in China and other countries; among these, acupuncture is one of the most popular measures. A number of clinical studies have been conducted to evaluate its efficacy [12-16]. Their results suggested that acupuncture is effective for pain relief in the immediate and short-term post-treatment period; however, the efficacy of a mid-term to long-term benefit for pain control or functional improvement was less clear [17-19]. Furthermore, comparative trials in the literature are few in number and of poor quality. Therefore, we will conduct a rigorous evaluation to test whether acupuncture performs better than placebo for treatment of CS neck pain.

The overall goal of this project is to determine the relative effectiveness and safety of acupuncture for CS neck pain.

## Methods/design

### Study design

This study will be a randomized, double-blind, parallel controlled clinical trial to evaluate the effectiveness and safety of acupuncture for CS neck pain. A total of 458 subjects with CS neck pain from outpatient clinics will be recruited and randomly allocated to either the active acupuncture group (experimental group) or the sham acupuncture group (control group). The Second People’s Hospital of Fujuan and the Affiliated Rehabilitation Hospital, Fujian University of Chinese Medicine will be responsible for recruiting, screening, and intervention of all patients and assessment of all outcomes. Management of the randomization sequence, blinding, and data analyses will be carried out by the Center for Evidence Based Medicine of Fujian Traditional Chinese Medicine University. Ethics approval has been received from Fujian Traditional Chinese Medicine University. Informed written consent will be obtained from all participants.

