### Randomization and allocation

The randomization schedule will be prepared by the Evidence-Based Medicine Center of the Academy of Integrative Medicine, Fujian University of Traditional Chinese Medicine. The specific randomization lists will be computer-generated using the SAS 8.12 software PLAY PLAN program (SAS software (Beijing) Co., Ltd, [name]) and concealed from the screeners, assessors, and patients by a designer from the Evidence-Based Medicine Center who is not involved in the study. Cards with group assignments and detailed treatment schedules will be prepared by the Evidence-Based Medicine Center and sealed in opaque envelopes. These sealed envelopes will be marked with the patients’ sequential numbers and kept by the screeners who are responsible for the screening of participants. When a patient has been enrolled, written informed consent has been obtained, and the patient has completed the baseline measurements and is confirmed to be an eligible participant, the envelope corresponding to the sequential number of the patient will be transmitted to the acupuncturist. The acupuncturist will open the envelope and perform the intervention (active or sham acupuncture) according to the treatment schedule written on the card. The information of the allocation list will remain confidential and kept by the acupuncturist not involved in participant recruitment or outcome assessment, and this information will not be shared with the data analyzers or outcome assessors.

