### Blinding

The outcome assessors will be blinded to the randomization allocation and will not be involved in performance of the interventions. Participants will be blinded to the group allocation and will not know whether they have been treated with active or sham acupuncture. It will be impossible to blind the acupuncturists because they will perform the interventional protocols. However, the acupuncturists will not take part in the outcome measurements or the statistical analyses, and will be requested not to disclose details about their treatment to the outcome assessors or participants. The statistician will be blinded to the group allocation until completion of the statistical analyses.

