### Active acupuncture

Active acupuncture treatment will be applied to the participants in the experimental group. Active acupuncture stimulation will be performed at the acupuncture points *Jing-jiaji* (EX-B2.C5), *Jing-jiaji* (EX-B2.C6), *Jing-jiaji* (EX-B2.C7), and *Jianzhongshu* (Sl15) on both sides of the body [22]. Sterile single-use acupuncture needles (40 mm in length and 0.30 mm in diameter; Hwato brand, Suzhou Medical Products Factory Co., Ltd., [name]) will be perpendicularly inserted to a depth of 20 to 30 mm at the selected stimulation point. When the treated participants achieve *de qi* sensation (soreness, numbness, distention, and heaviness), electroacupuncture with its anode connected to *Jing-jiaji* (EX-B2.C5) and cathode connected to *Jing-jiaji* (EX-B2.C7) will be performed to stimulate the relevant acupuncture points for 20 minutes by a single experienced acupuncturist using a continuous-wave, 1-Hz frequency and a comfortable strength.

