### Intervention regimen

Patients will be required undergo ten treatment sessions at a frequency of five sessions a week, and the intervention will be completed in 2 weeks. All electroacupuncture procedures will be performed with a Hwato brand SDZ-II electronic needle therapy instrument made by Suzhou Medical Products Factory Co., Ltd. The two groups will be separated from the treatment, which will be performed by a single acupuncturist.

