### Statistical analysis

The primary outcomes will undergo intent-to-treat analysis based on the initial treatment assignment and focus on assessment of the main effects of the acupuncture treatment for CS at symptoms of CS and function of the cervical vertebrae. Analyses will be performed using IBM SPSS 20 (version 20.0, IBM Corp., New York, NY, USA). The continuous variables and descriptive values will be expressed using means with standard deviations or medians with ranges. For the variables with a normal distribution, statistical comparisons between the groups will be made by using a *t* test. If the variables have a non-normal distribution or ordinal level, statistical comparison between groups will be made using the Mann–Whitney *U* test. Measures with a discrete distribution will be expressed as percentages and analyzed by the *χ*^2^ or Fisher’s exact test as appropriate. The amount of extra diclofenac sodium used between the experiment and control groups will be analyzed, and a general linear model will be applied to adjust its confounding influence if necessary.

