## Discussion

In this randomized, double-blind controlled trial of patients with CS neck pain, we intend to investigate the mid-term efficacy and safety of acupuncture for CS neck pain. This is a well designed study in strict accordance with the Consolidated Standards of Reporting Trials (CONSORT) statement of randomized controlled trials and will enable determination of the effects of acupuncture [25]. First, we estimated the most optimal sample size to ensure adequate test performance. Second, we ensured that this study is truly a randomized controlled trial to the greatest extent possible by full implementation of randomization and blinding. In addition, to assess the efficacy of acupuncture for CS neck pain, the placebo effect should be avoided. At present, ‘sham acupuncture’ is considered to be the most commonly proposed placebo control. In this protocol, sham acupuncture is applied by adapting the depth of needling at non-acupuncture points. This technique has been widely used in clinical trials, many of which have adopted this method as a control [26-30]. Its main advantages are that it is the strongest type of patient blinding and is easy to carry out. Its main problem is that the control group may play a role in the treatment of the disease; thus, the effect of acupuncture maybe be underestimated [31]. However, if the experimental results prove that acupuncture is indeed better than the control group treatment, the efficacy of acupuncture for CS neck pain will be positive. In terms of evaluation indicators, we will use a reasonable specification, design a rigorous professional scale as the evaluation indicator of the primary outcome, and avoid a subjectively developed fuzzy classification evaluation, distorting data less and reducing bias. The interventions (active or sham acupuncture) will be performed by a fixed chief physician, who has more than 20 years of clinical experience. This will improve the participants’ compliance and reduce the risk of dropout.

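### Two hospitals recruit, treat and assess, but the stated primary comparison has no hospital term: a small, avoidable loss of precision, not a bias

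*Protocol article*

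**What the plan says.** - **Two sites.** Study design says that the two hospitals "will be responsible for recruiting, screening, and intervention of all patients and assessment of all outcomes".
- **Comparison.** For normally distributed variables, Statistical analysis says that "statistical comparisons between the groups will be made by using a" t test. For non-normal or ordinal variables it names the Mann–Whitney U test. The one adjustment mentioned is a general linear model for extra diclofenac use, if needed. Hospital does not appear.
- **Allocation.** Randomization and allocation describes computer-generated lists and opaque envelopes: "These sealed envelopes will be marked with the patients’ sequential numbers and kept by the screeners". It does not say whether lists or envelopes are separate by hospital.
- **Operator.** Active acupuncture has stimulation given "for 20 minutes by a single experienced acupuncturist". Intervention regimen describes treatment "which will be performed by a single acupuncturist". The Discussion says that both interventions "will be performed by a fixed chief physician, who has more than 20 years of clinical experience". Blinding uses the plural: "It will be impossible to blind the acupuncturists because they will perform the interventional protocols".

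**The concern.** In a two-hospital trial, patients at one site may score differently on the NPQ from patients at the other, through referral pattern, severity or the way assessments are made. Neck function is the other primary outcome, and outcome assessors rate it by physical examination, so a site difference is plausible there too. The documents do not say that such a difference exists.

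If it does exist, a two-group test that ignores hospital leaves the between-hospital variation in the residual. It also leaves uncorrected any chance difference between arms in the share of patients from each hospital. Hospital is known for every patient, so this variation can be removed at almost no cost. The trial is sized for 80% power with no margin, so even a small loss is worth avoiding.

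**Working it through.** **Inputs from Sample size:** planning means 24.04 and 20.71, difference 3.33; SDs 11.83 and 11.91, pooled 11.87; two-sided alpha 0.05; power 80%; 198 per group; 15% dropout; total 456. Study design gives 458; I use 456.

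**The plan's own figure.** n per group = 2 × (1.960 + 0.842)² × 11.87² / 3.33² = 199.5, so 200, against 198 stated. With SD 11.83 it is 199. The stated figure reproduces to within two patients. The total is 198 × 1.15 × 2 = 455.4, rounded up to 456.

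**Completers.** 456 × 0.85 / 2 = 193.8, so 194 per arm.

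**Power with hospital in the model.** Take 11.87 as the within-hospital SD. SE = 11.87 × √(2/194) = 1.205. Then 3.33 / 1.205 − 1.960 = 0.803, which gives 78.9%.

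**Power without hospital.** The documents give neither the hospital difference D nor the hospital shares p and 1 − p, so both are assumed. The total SD is √(11.87² + p(1 − p)D²). With p = 0.5:

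| Assumed D (NPQ points) | Total SD | Power without hospital | Loss against 78.9% |
|---|---|---|---|
| 2 | 11.91 | 78.6% | 0.3 points |
| 5 | 12.13 | 77.1% | 1.8 points |
| 8 | 12.53 | 74.5% | 4.4 points |

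An uneven split shrinks the loss. For D = 5, power without hospital is 77.4% at 70:30 and 78.3% at 90:10.

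If 11.87 is instead read as the total SD, already containing hospital variation, the plain test has 78.9% power. The hospital term then raises it to 79.2%, 80.7% or 83.5% for D = 2, 5 or 8 (50:50 split). The gain is of similar size on either reading.

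**Chance imbalance if allocation is not by hospital.** With 228 per arm and p = 0.5, the SE of the between-arm difference in hospital share is √(2 × 0.25/228) = 0.0468. The 95% range is ±1.96 × 0.0468 = ±9.2 percentage points. Multiplied by D, the NPQ contrast shifts by up to ±0.18, ±0.46 or ±0.73 points for D = 2, 5 or 8. For scale, ordinary sampling error at 228 per arm has a 95% half-width of 1.96 × 11.87 × √(2/228) = 2.18. Adding 0.46 in quadrature gives √(2.18² + 0.46²) = 2.23, about 2% wider.

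**Type I error.** In 10,000 simulated trials of 456 patients with no treatment effect, a 5-point hospital difference and allocation ignoring hospital, the plain t test rejected in 4.9%. The nominal level holds.

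**The case against.** The strongest reply is that this hardly matters. The hospital difference and the split are both assumed, and a 5-point difference exceeds the 3.33-point treatment effect. Randomisation keeps the estimate unbiased, and the error rate of the t test already allows for chance imbalance. Choice of covariates is also commonly left to a statistical analysis plan, which is not shown. The points on size and bias stand, and they set the weight of this comment. The point on covariates stands only in part: the article is not silent on the primary comparison. It names the tests and one possible adjustment, and hospital is not included. If the full plan already has a hospital term, only the article's wording needs aligning.

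A reader might infer two stronger criticisms, and the documents support neither.

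- **That randomisation ignores hospital.** The article does not say so. It mentions lists in the plural and numbered envelopes, and it neither states nor excludes separation by hospital.
- **That operators differ between hospitals, so that operator and hospital coincide.** Active acupuncture, Intervention regimen and the Discussion all describe one operator, and Randomization and allocation also uses the singular. Only Blinding uses a plural, in a general sentence about why that role cannot be blinded. If there is one operator, operator differences cannot arise. Each patient has "ten treatment sessions at a frequency of five sessions a week", so covering two hospitals may be demanding. But the article gives no caseload, recruitment period or treatment location from which to conclude that one person could not do it.

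**Conclusion.** The point holds as a matter of precision. Two hospitals supply, treat and assess the patients, and the stated primary comparison leaves hospital out. For an assumed 5-point NPQ difference between hospitals and an even split, this costs about 1.8 percentage points of power (78.9% to 77.1%). The cost is 0.3 points for a 2-point difference and 4.4 points for an 8-point difference. It is smaller if one hospital recruits most patients and nil if the hospitals do not differ. There is no systematic bias and no inflation of type I error, so a result from the plain test would still be valid. No figure can be given for neck function, because the article states no planning values for it. The mismatch between singular and plural acupuncturists is a minor matter of wording.

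**What to change.** 1. **Analysis.** Analyse the primary outcomes with a linear model that has treatment and hospital as fixed factors. Where a rank test is needed, use a hospital-stratified one such as the van Elteren test. Fix this before allocation is revealed to the statistician.
2. **Allocation.** State whether the lists and envelope series are separate by hospital. If they are not, use hospital-specific lists for the remaining recruitment.
3. **Wording.** Reconcile the plural in Blinding with the single operator in Active acupuncture, Intervention regimen and the Discussion.

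The cost is one degree of freedom in the model, possibly a second envelope series, and a line of text. No extra patients are needed. Because recruitment is under way, patients already randomised would be covered only by the hospital term in the analysis.

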### Participants

We will include patients between 18 and 60 years of age with CS neck pain. Patients must have typical symptoms of neck pain and stiffness, but their cervical vertebrae must be normal or show only physiological curvature changes on radiographic examination. Potentially eligible participants are being identified through screening of patient medical records at the participating hospitals. Screening of patients will be performed by one of the authors according to the inclusion and exclusion criteria. A flow diagram of the patients is shown in Figure 1.

**Figure 1 F1:**
[figure not shown]
Flow diagram of participants.

### Inclusion criteria

To be eligible, participants must fulfill the following criteria: (1) a confirmed diagnosis of CS neck pain in accordance with the diagnostic criteria published by the Chinese Association of Rehabilitation Medicine (2010) [20] and with reference to the *International Classification of Diseases,* 10th edition (ICD-10) codes (http://www.icd10data.com): M47.812 (other spondylosis without myelopathy or radiculopathy (cervical region)); (2) male or female 18 to 60 years of age; (3) with/without positive signs of musculoskeletal system upon physical examination; (4) pain intensity ranging from 3 to 7 points on a visual analog scale (VAS) upon recruitment; (5) no acupuncture or other relative treatment within the last 7 days; and (6) informed consent document has been signed.

### Exclusion criteria

The exclusion criteria were as follows: (1) history of neck trauma or T1 to T6 thoracic vertebra trauma; (2) has vertebral body or spinal canal cancer, tuberculosis, or severe osteoporosis; (3) history of neck surgery or presence of congenital malformation of the cervical vertebrae; (4) pregnant or lactating (women) or presence of a mental disorder; (5) has a severe systemic disease such as cardiocerebrovascular disease, tumors, diabetes mellitus, kidney disease, or digestive system disease; (6) inability to complete research questionnaires; and (7) rejection of randomization.

### Sample size

The sample size calculation was based on a reference of a similar intervention in similar patient groups using the same primary outcome instrument [21]. The primary outcome measure is improvement of scores in neck pain as measured with the Northwick Park Neck Pain Questionnaire (NPQ) at the end of treatments. According to previous research [21], the mean and standard deviation of NPQ scores were (24.04 ± 11.83) in the placebo group and (20.71 ± 11.91) in the acupuncture group. The sample size was calculated based on the formula:

(1)$$n_{1}=n_{2}=2{\left(\frac{z_{\alpha /2}+z_{\beta }}{M_{e}-M_{c}}\right)}^{2}\delta^{2}$$

with a type I error of 5% (α = 0.05) and 80% power (β = 0.2). A total of 198 patients are required in each group to show statistical differences between the groups. We estimated that 15% patients will drop out of the study; thus, 456 patients was established as the sample size.

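### 456 patients less the planned 15% dropout leave about 194 per group, not the 198 required, and the total is given as 458 elsewhere

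*Protocol article*

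**What the plan says.** The Sample size section bases the calculation on the NPQ at the end of treatment. From one previous study it takes a mean of 24.04 (SD 11.83) under placebo and 20.71 (SD 11.91) under acupuncture. It uses the usual normal-approximation formula for two equal groups, with a two-sided 5% type I error and 80% power. The formula contains a single SD, and the text does not say which of the two was used.

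The result is stated as "A total of 198 patients are required in each group to show statistical differences between the groups". The dropout allowance follows: "We estimated that 15% patients will drop out of the study; thus, 456 patients was established as the sample size".

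The Abstract (Methods/Design) repeats that total: "A total of 456 patients with neck pain caused by cervical spondylosis". The Study design section gives a different one: "A total of 458 subjects with CS neck pain from outpatient clinics will be recruited". Nothing in the article explains the difference of two. Trial status reports that recruitment is under way.

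**The concern.** The section names a required number per group and an expected loss, and presents the total as following from them. Read in the ordinary way, as 15% of the patients enrolled, that loss takes 456 below the number required. A common slip produces exactly this pattern: the required number is raised by 15% when it should be divided by the 85% expected to remain.

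Separately, the number to be randomised is stated in two ways in current text. A reader comparing the final report with the plan could not tell which target applied.

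At stake is whether 80% power, 15% dropout and 456 patients can all be claimed together, and whether the trial has one recruitment target.

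**Working it through.** **Inputs (Sample size section).** Difference = 24.04 − 20.71 = 3.33. SD 11.83 (placebo) or 11.91 (acupuncture); pooled SD = √((11.83² + 11.91²)/2) = 11.87. Two-sided α = 0.05, power 80%, dropout 15%.

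**Step 1: reproduce 198.** n per group = 2 × ((z₁ + z₂)/difference)² × SD².

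- Placebo SD with tabled values 1.96 + 0.84 = 2.80: 2 × (2.80/3.33)² × 11.83² = 197.9, which rounds up to 198.
- Placebo SD with unrounded z values: 198.1.
- Pooled SD: 199.5. Acupuncture SD: 200.8.

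So 198 is reproduced with the placebo SD and the usual tabled z values.

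**Step 2: reproduce the totals.**

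- 198 × 1.15 = 227.7, rounded up to 228 per group; 2 × 228 = 456. This matches the Sample size section and the Abstract exactly.
- 199 × 1.15 = 228.85, rounded up to 229 per group; 2 × 229 = 458. This matches the Study design section exactly, if 198.1 is rounded up to 199 first.

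The article prints neither multiplication. Both are inferred from the match.

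**Step 3: apply the 15% loss.**

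| Randomised | Left after 15% loss | Per group | Loss that still leaves 198 per group |
|---|---|---|---|
| 456 | 456 × 0.85 = 387.6 | 193.8 | 1 − 198/228 = 13.2% |
| 458 | 458 × 0.85 = 389.3 | 194.7 | 1 − 198/229 = 13.5% |
| 466 | 466 × 0.85 = 396.1 | 198.05 | 1 − 198/233 = 15.0% |

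The last row comes from 198/0.85 = 232.9, rounded up to 233 per group. It is 10 more than 456 and 8 more than 458. The shortfall in this table does not depend on how 456 was obtained.

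**Step 4: the cost in power.** Normal formula: power = Φ(difference/(SD × √(2/n)) − 1.96).

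- n = 198, SD 11.83: 3.33/(11.83 × √(2/198)) = 2.801; Φ(0.841) = 80.0%.
- n = 194, SD 11.83: 3.33/(11.83 × √(2/194)) = 2.772; Φ(0.812) = 79.2%.

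| Basis | 198 per group | 194 per group |
|---|---|---|
| Normal formula, SD 11.83 (the plan's basis) | 80.0% | 79.2% |
| Normal formula, pooled SD 11.87 | 79.7% | 78.9% |
| Noncentral t, pooled SD 11.87 | 79.5% | 78.7% |

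On every basis the dropout step costs about 0.8 percentage points. The remaining differences between rows come from the choice of SD and distribution.

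**The case against.** **The effect is trivial.** Ten patients are 2.2% of 456, and the inputs are themselves estimates from a single earlier study. This stands: nothing in the design or its likely conclusions turns on 0.8 points of power.

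**194 per group is a worst case for the primary outcome.** The sample size rests on the NPQ at the end of treatment, day 14 in Table 1. The 15% refers to dropout from the study, which continues by telephone to day 98. A patient lost after day 14 has already given the NPQ value that matters, and the plan does not divide dropout by time. This also stands: the loss of power is conditional on all 15% being lost by day 14. It does not rescue the statement itself, which sets 15% dropout against 198 per group without any such qualification.

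**The inflation step is not printed.** True, and the multiplication by 1.15 should be called an inference. The shortfall needs only the stated 456, 15% and 198.

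**Readings that go too far.** A reader might infer that 198 is itself too low, because the pooled or acupuncture SD gives 199.5 or 200.8. The documents do not support this: the formula has one unlabelled SD, and the placebo SD with tabled z values gives 197.9. A reader might also take 458 for a number without any derivation and therefore the misprint. It has a plausible one (199 × 1.15, rounded up and doubled), so the text does not show which total was intended.

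**Conclusion.** The point holds as an internal inconsistency. As written, the Sample size section claims that 456 patients with 15% dropout leave 198 per group; they leave about 194. The alternative total of 458 leaves about 195 and does not cure the shortfall, so settling on either figure is not enough without also restating the allowance.

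The shortfall is 10 patients against 466. Power at about 194 per group is roughly 79% (79.2% on the plan's formula with SD 11.83; 78.7% with noncentral t and pooled SD 11.87). This assumes that the 15% is a share of those randomised, is equal in the two groups, and falls wholly before the end-of-treatment NPQ.

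It would be wrong to conclude that the trial is materially underpowered or that it must recruit more patients. The correction is worth making because the two totals contradict each other while recruitment is under way, and because the stated combination of power, dropout and sample size does not hold.

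**What to change.** 1. Use one total in the Abstract, Study design and Sample size sections. The sponsor should confirm whether 456 or 458 was the target; the article does not settle it.
2. Restate the dropout sentence so that its figures agree. For 456, for example: with 456 patients randomised (228 per group), 198 per group remain if dropout before the end-of-treatment NPQ is no more than about 13.2%; if it reaches 15%, about 194 per group remain and power is about 79%. For 458 the tolerated dropout is about 13.5%, and about 195 per group remain at 15%.
3. Name the SD used in the formula. The placebo SD, 11.83, is the one that reproduces 198.

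The cost is a few lines of text and a slightly less favourable stated power or dropout tolerance. No added patients are needed.
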